# Prevention of sickness absence through early identification and rehabilitation of at-risk patients with musculoskeletal pain (PREVSAM): a randomised controlled trial protocol

**DOI:** 10.1186/s12891-020-03790-5

**Published:** 2020-11-28

**Keywords:** Musculoskeletal, Prevention, Rehabilitation, Interdisciplinary, Sick leave, Intervention, Randomised

## Abstract

**Background:**

Musculoskeletal pain is globally a leading cause of physical disability. Many musculoskeletal-related pain conditions, such as low back pain, often resolve spontaneously. In some individuals, pain may recur or persist, leading to ong-term physical disability, reduced work capacity, and sickness absence. Early identification of individuals in which this may occur, is essential for preventing or reducing the risk of developing persistent musculoskeletal pain and long-term sickness absence. The aim of the trial described in this protocol is to evaluate effects of an early intervention, the PREVSAM model, on the prevention of sickness absence and development of persistent pain in at-risk patients with musculoskeletal pain.

**Methods:**

Eligible participants are adults who seek health care for musculoskeletal pain and who are at risk of developing persistent pain, physical disability, and sickness absence. Participants may be recruited from primary care rehabilitation centres or primary care healthcare centres in Region Västra Götaland. Participants will be randomised to treatment according to the PREVSAM model (intervention group) or treatment as usual (control group). The PREVSAM model comprises an interdisciplinary, person-centred rehabilitation programme, including coordinated measures within primary health care, and may include collaboration with participants’ employers. The primary outcome sickness absence is operationalised as the number and proportion of individuals who remain in full- or part-time work, the number of gross and net days of sickness absence during the intervention and follow-up period, and time to first sickness absence spell. Secondary outcomes are patient-reported short-term sickness absence, work ability, pain, self-efficacy, health-related quality of life, risk for sickness absence, anxiety and depression symptoms and physical disability at 1 and 3 months after inclusion (short-term follow-up), and at 6 and 12 months (long-term follow-up). A cost-effectiveness analysis is planned and drug consumption will be investigated.

**Discussion:**

The study is expected to provide new knowledge on the effectiveness of a comprehensive rehabilitation model that incorporates early identification of patients with musculoskeletal pain at risk for development of sickness absence and persistent pain. The study findings may contribute to more effective rehabilitation processes of this large patient population, and potentially reduce sickness absence and costs.

**Trial registration:**

ClinicalTrials.gov Protocol ID: NCT03913325, Registered April 12, 2019.

Version 2, 10 July 2020.

Version 2 changes: Clarifications regarding trial aim and inclusion process.

## Background

The increasing burden from musculoskeletal disorders has been shown in the 20-year follow-up of the Global Burden of Disease Study (GBDS) and, even though musculoskeletal pain rarely is fatal, it threatens peoples’ health and account for a large amount of disability adjusted life years (DALYs) [1]. Approximately 10% of individuals who suffer from musculoskeletal pain develop disabling persistent problems, and, as such, are at increased risk of long-term sickness absence [2]. In Sweden, almost half of all ongoing sickness benefits reimbursed by The Swedish Social Insurance Agency (SSIA) relate to musculoskeletal disorders and mild to moderate mental illnesses [3]. Even though there has been a focus on return to work for many years in Sweden, yielding governmental support, recent years have seen an increase in sickness absence. Between 2010 and 2016 sickness cash benefits increased by 80% [4]. Musculoskeletal conditions accounted for 19% of all sick-leave cases among women and 24% of all cases among men, and were more common in people older than 50 years. However, in the beginning of 2017 a decrease was seen [4]. Persistent pain and reduced work capacity have been shown to be strongly associated, and the probability for disability pension or unemployment is significantly higher for individuals with persistent pain [5]. Subsequently, there is increasing consensus that there is a need for early identification and prevention of the development of persistent pain, and to prevent reduced work ability that may lead to sickness absence.

Musculoskeletal pain is also a common reason for consulting primary health care [6], at substantial costs, creating a demand on the healthcare system to provide accurate and timely diagnosis and treatment. This underscores the need for early identification of individuals at risk of developing persistent pain, which might not only require prolonged contact with healthcare services but potentially lead to sickness absence due to reduced work ability.

A systematic review from The Swedish Health Technology Assessment [7] aimed to provide evidence-based practice recommendations for interventions in the acute and subacute phase of neck and back pain, preventive for persistent pain. However, it was not possible to draw such conclusions as the included studies compared different combinations of interventions in a way that made it unclear which of the measures taken were actually preventive. The review concluded that more rigorous and scientifically sound studies were needed.

Nevertheless, psychosocial factors, independently as well as in interaction with physical factors, have been shown to be associated with risk of sickness absence [8], and a biopsychosocial approach using interdisciplinary teamwork seems well suited for conditions that already are, or are at risk of becoming, chronic [9, 10].

A person-centred approach and shared decision making are widely advocated as key components of effective illness management [11]. Even though more research is needed, it seems that a person-centred approach could positively affect rehabilitation outcomes [12]. It has been shown to improve self-efficacy in patients with acute coronary syndrome when used throughout the chain of care from hospital to primary care [13] and also to improve health-related quality of life when used in a prehabilitation program for patients scheduled for lumbar fusion surgery [14].

An important factor shown to be related to better functioning outcome in patients with persistent pain is high self-efficacy [15]. Self-efficacy refers to the confidence that one has in one’s capabilities to successfully execute a course of action to a desired outcome [15]. Patients with musculoskeletal disorders have reported a preference for participating and sharing clinical decision making with their rehabilitation professional, and participating in clinical decision making has been suggested to lead to the patient’s active engagement in their rehabilitation [16]. Patients with a higher degree of personal responsibility were more likely to report a better outcome of physiotherapy treatment [17]. However, it also has been shown that peoples’ willingness to take responsibility for the management of musculoskeletal pain should not be underestimated. Patients have described how the responsibility should be shared with the medical professionals but also identified and met by society, employers and family [18].

Poor communication and information exchange have been reported as important barriers for effective collaboration among different health and welfare services [19]. It has been reported that the collaboration between health care and employers is to be difficult to achieve, that the relationships with the social insurance officers is often strained, and this is affecting collaboration among the three parts [20]. A systematic review [21] on the effectiveness of workplace interventions in return to work for musculoskeletal pain recommended implementing multi-domain interventions (i.e. with healthcare provision, service coordination, and work accommodation components). The planned study will draw on these findings to establish responsibilities, clear roles, and routines for communication and collaboration among the patient, employer and other stakeholders.

The use of cognitive behavioural therapy (CBT) based strategies in physiotherapy interventions has been shown to be beneficial for preventing persistent low back pain [22]. Adding a psychological intervention (generally CBT) to physiotherapy for patients with persistent pain has been shown in a systematic review and meta-analysis to significantly improve physical function and quality of life compared with physiotherapy alone [23]. The psychological component was generally delivered by clinical psychologists, implying that their training and skill set likely is necessary to achieve the desired outcome. Many other studies also have contributed to establishing a solid evidence base for CBT as treatment for persistent pain, suggesting that it also would be beneficial for those at risk of developing persistent pain [24, 25]. Hence, there still is a gap in knowledge on how to prevent the development of persistent musculoskeletal pain and the subsequent limitations in daily life. The planned study will include early access to psychological intervention.

To conclude, sickness absence due to persistent musculoskeletal pain is complex; therefore a rehabilitation model was designed to provide an early intervention for prevention of sickness absence for musculoskeletal pain, called the PREVSAM model. The model incorporates a person-centred approach in a biopsychosocial model using interdisciplinary teamwork and possible collaboration with the workplace, where clear assignments of who is responsible for what actions are set. The model will be evaluated in a randomised controlled trial.

### Aims

The aim of the study is to evaluate effects of an early intervention, the PREVSAM model, on the prevention of sickness absence and development of persistent pain in at-risk patients with musculoskeletal pain. The study will also evaluate effects of the PREVSAM model on patient-reported work ability, risk for sickness absence, musculoskeletal pain status, self-efficacy, health-related quality of life, physical disability, depression and anxiety symptoms, and drug consumption. Cost-effectiveness of the model will be evaluated.

Research questions:

Q1: Is the PREVSAM model more effective in preventing sickness absence, compared with treatment as usual, in patients with musculoskeletal pain who have been identified to be at risk for sickness absence?

Q2: Do patients participating in the PREVSAM model report higher work ability, improved pain status, better self-efficacy, less physical disability or higher health-related quality of life, compared with those who receive treatment as usual at follow-up?

Q3: Is there a patient-reported reduced risk (using the ÖMPSQ score) for sickness absence in patients participating in the PREVSAM model, compared with those who received treatment as usual at follow-up?

Q4: Can any effects be seen in regard to anxiety and depression symptoms or drug consumption in patients participating in the PREVSAM model, compared with those who receive treatment as usual?

Q5: Is the PREVSAM model more cost-effective compared with treatment as usual?

The study hypothesis is that a person-centred rehabilitation, illuminating and emphasizing responsibilities, using interdisciplinary teamwork which can also include collaboration with the employer and/or workplace, in an early stage before symptoms are manifest and consequences in form of sickness absence have become established, will be more effective than treatment as usual in prevention of sickness absence.

## Methods

This randomised controlled trial has been registered with ClinicalTrials.gov, Protocol ID: NCT03913325, initial release 12/04/2019.

### Study design

A randomised, controlled, two-armed, superiority trial will be conducted, in which treatment according to the PREVSAM model (intervention group) is compared with treatment as usual (TAU) (control group). Findings will be reported according to the CONSORT Checklist. The study design is illustrated in Fig. 1.

**Fig. 1 Fig1:**
[figure not shown]
Flow chart of participants through the study

### Study population and setting

Adult individuals in Region Västra Götaland who seek health care for musculoskeletal pain at primary care rehabilitation centres or primary care healthcare centres are potentially eligible for inclusion. A list of study centres will be available from the corresponding author on request. Inclusion and exclusion criteria for study participation are described in Table 1.

**Table 1 Tab1:** Inclusion and exclusion criteria for study participation

*Inclusion criteria*	*Exclusion criteria*
Aged ≥18 years	Pain not primarily generated from the musculoskeletal system
Understand Swedish sufficiently to be able to fill out the questionnaires	Sickness cash benefit more than 30 days during the last 12 months due to musculoskeletal pain
Having a paid job or receiving parental leave benefits, unemployment benefits or student aid	Full disability pension or retired due to age
Musculoskeletal pain for less than 3 months during the current episode	Pregnancy
Risk for development of persistent musculoskeletal pain and disability, indicated by a score ≥ 40 on the ÖMPSQ-SF	Red flag disorders such as malignancy/ cancer, acute major traumas such as multiple fractures (less than 6 months ago) or infection, spinal cord compression/cauda equina
Independently mobile (with or without aids), to be capable of participating in intervention	Severe mental illness, ongoing substance abuse disorders

For inclusion, participants will be screened using the Örebro Musculoskeletal Pain Screening Questionnaire Short Form (ÖMPSQ-SF) [26]. A total score below 40 points on the ÖMPSQ-SF indicates a low risk for development of manifest problems and sickness absence, while scores over 40 points indicate an increased risk. In the screening process we will select individuals with ÖMPSQ-SF score equal to or greater than 40.

### Recruitment

All public rehabilitation centres and a majority of the private rehabilitation centres in the Region Västra Götaland’s Care choice primary care, have been informed about the study and invited to participate. We expect approximately 10 rehabilitation centres to be interested in participating and, during 2019, we have established contact with the participating centres and provided the necessary infrastructure for support of patient recruitment and intervention. To achieve adequate participant enrolment and reach the target sample size, additional centres may be added (from primary care rehabilitation centres or primary care healthcare centres). Interdisciplinary teams are formed by healthcare professionals at the participating centre or can be complemented by a consultant.

Patients at the participating centres will be screened for eligibility. Those fulfilling the inclusion criteria will be provided with oral and written information before asked to participate. Those accepting participation will complete a written informed consent form.

### Randomisation

The participants will be randomised to either the PREVSAM model or to treatment as usual (TAU). Sequentially numbered, opaque, sealed envelopes containing notes marked ‘PREVSAM’ or ‘TAU’ are block-randomised by a computer programme in blocks of six (three of each), in order to ensure an even distribution. These are placed in a box at each participating centre. The allocation sequence will not be accessible to the persons who enrol participants and assign intervention. Enrolment and assignment of intervention will most often be done by a person from the interdisciplinary team.

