### Blinding

Due to the nature of the intervention, neither participating healthcare professionals nor patients will be blinded to treatment. Investigators, outcome assessors and data analysts will be blinded to group allocation.

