### Intervention: the PREVSAM model (intervention group)

The PREVSAM model includes:
a person-centred approachidentification of the patient’s attitudes towards responsibility for the management of musculoskeletal pain and clarification of responsibilities for the individual, health care, employer/Swedish public employer servicestructured, individualised, synchronised, rehabilitation based on interdisciplinary teamwork, continuous communication and regular coordination among all stakeholders, and a mutual philosophy of rehabilitationearly access to psychologist or psychotherapist to address psychosocial factorspossibility of early contact and collaboration with employer/workplace before sickness absence has occurred.

The person-centred approach entails planning the rehabilitation together in partnership with the individuals, and taking their resources and wishes into consideration [27]. Individualised, person-centred, rehabilitation within the PREVSAM model will be based on the patient’s narrative and constructed together with the interdisciplinary team based on the patient’s goals, attitudes of responsibility, and physical, psychological, and social resources. Workplace preconditions will be assessed, preferably based on the Convergence Dialogue Meeting [28] also used in a previous rehabilitation study [29], and employer responsibility will be highlighted, based on the Organisational and social work environment provisions from the Swedish Work Environment Authority (AFS 2015:4). Responsibilities for the different parts of the participant’s rehabilitation will be clearly assigned to the individual, health care, and employer or Swedish public employer service.

The interdisciplinary team is an important component of the PREVSAM model and will be comprised of the patient, a physiotherapist, an occupational therapist, and a psychologist/psychotherapist. If needed, contact with a general practitioner will be provided. If orthopaedic consultation or further investigations are needed, the participant can be referred to a physiotherapist with experience in orthopaedic triage for assessment and further management.

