### Dissemination and implementation of study findings

This study protocol will be published in an open access journal to allow free public access. The study findings will be disseminated and made publicly available in peer-reviewed publications and conference presentations. The results will also be disseminated, through regular dissemination and communication channels, within and outside health care and university contexts. The Swedish research Council for Health, Working Life and Welfare that sponsors the study usually organises conferences to disseminate results from studies they sponsor. Since the planned study focuses on collaboration both within health care and with employers and the SSIA, communication strategies targeting these stakeholders will be developed.

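### A constant, published block of six, held at each centre and handled by the unblinded intervention team, lets an enroller who keeps count deduce the ends of blocks

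*Protocol article*

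**What the plan says.** The relevant statements are in the protocol article, mostly under Randomisation.

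- **Block scheme.** The notes "are block-randomised by a computer programme in blocks of six (three of each), in order to ensure an even distribution".
- **Concealment.** The device is "Sequentially numbered, opaque, sealed envelopes containing notes marked" with the arm. Of the envelopes it says: "These are placed in a box at each participating centre". It adds: "The allocation sequence will not be accessible to the persons who enrol participants and assign intervention".
- **Who enrols.** "Enrolment and assignment of intervention will most often be done by a person from the interdisciplinary team". Under Intervention, that team is part of the treatment under test: "The interdisciplinary team is an important component of the PREVSAM model".
- **Blinding.** "neither participating healthcare professionals nor patients will be blinded to treatment". Investigators, outcome assessors and data analysts are to be blinded.
- **Publication.** Under Dissemination: "This study protocol will be published in an open access journal to allow free public access". The block size is therefore public.

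The article describes no varying block size and no central allocation.

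**The concern.** In a trial whose treating staff know who received what, concealment depends on the next allocation being unpredictable as well as unread. Here the block size is constant and public, the sequence runs within one centre, and the usual enroller belongs to the team that delivers one of the two arms. Someone who has counted three of one arm in the current block knows all that remains of it.

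An enroller who knows or suspects the next arm can choose whom to invite and when. If that choice is related to the patient's risk of sickness absence, the arms differ at entry. Registry outcomes, blinded assessors and intention-to-treat analysis all act after entry and cannot undo this. The covariate adjustment planned under Statistical analyses can reduce imbalance in measured factors only.

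**Working it through.** The protocol gives no figure for predictability, so there is none to reproduce.

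**Inputs.** Block of six, three per arm (Randomisation). 200 per group, so 400 in total (Statistical analyses). About 10 centres (Recruitment), so 400 / 10 = 40 patients per centre on average.

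**Assumptions.** The enroller knows the block size and all earlier allocations at the centre, and each box holds whole blocks. The document states neither that enrollers keep such a count nor that boxes hold whole blocks.

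**Allocations certain in advance.** There are C(6,3) = 20 equally likely blocks. A position is certain once one arm is used up.

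| Position | Probability that it is certain | Reason |
|---|---|---|
| 1 to 3 | 0 | no arm can be used up yet |
| 4 | 2/20 = 0.10 | first three all in one arm |
| 5 | 8/20 = 0.40 | three of the first four in one arm |
| 6 | 1.00 | always |

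The sum is 1.5 of 6, or 25%. The closed form for n per arm agrees: 2n/(n+1) = 6/4 = 1.5. Over 400 patients in complete blocks that is 100 allocations.

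**At 40 patients per centre.** A centre fills six blocks and four places of a seventh: 6 × 1.5 + 0.1 = 9.1 of 40, or 22.75%. Over 10 centres that is 91 of 400.

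**Best guessing.** The rule is to name the arm with more notes left in the block, and to toss a coin when they are equal. The chance of being right at positions 1 to 6 is:

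- Position 1: 0.5
- Position 2: 3/5 = 0.6
- Position 3: 0.4 × 0.75 + 0.6 × 0.5 = 0.6
- Position 4: 0.1 × 1 + 0.9 × 2/3 = 0.7
- Position 5: 0.4 × 1 + 0.6 × 0.5 = 0.7
- Position 6: 1

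The sum is 4.1 of 6, or 68.3%, against 50% by chance. At 40 per centre it is 6 × 4.1 + (0.5 + 0.6 + 0.6 + 0.7) = 27.0 of 40, or 67.5%.

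**Effect of varying the block size.** A simulation of 3,000 centres of 40 patients used an enroller who updates optimally. In the varying scheme this enroller knows the set of sizes but not which one is in use.

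| Scheme | Certain in advance | Best guess right |
|---|---|---|
| Fixed 6 | 22.7% | 67.5% |
| Random 4, 6 or 8 | 2.3% | 67.6% |

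Varying the size removes most of the certainty but leaves the best-guess rate unchanged.

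**The case against.** Numbered, opaque, sealed envelopes and a withheld list are real safeguards against reading ahead. The protocol's statement that enrollers have no access to the sequence is not shown to be false: deducing the end of a block differs from having the list. A reader might infer a false statement by the protocol, but the text does not support that.

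The document also does not show that anyone keeps a tally. Several people may enrol at one centre, most often is not always, and that the team member opens the envelope is inferred from the word assignment. Whole blocks per box are likewise inferred, from the separate boxes and the aim of even distribution. Part-filled blocks lower the certain share, and Recruitment allows centres to be added.

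Discretion over entry is limited. Eligibility rests on a self-completed ÖMPSQ-SF score of at least 40 and on largely factual criteria (Table 1). Planned adjustment can also address measured imbalance.

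These points stand as limits on the finding. They do not remove it: not inviting or deferring a patient needs no breach of the criteria, and none of these safeguards prevents counting within a block of known, constant size.

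**Conclusion.** The weakness holds as a risk. With a constant, public block of six at each centre, an enroller who tracks past allocations can know up to 25% of allocations beforehand (about 23%, or 91 of 400, at 40 per centre) and can guess about 68% correctly. Both figures rest on whole blocks per box and a complete count of earlier allocations, so they are upper figures for what enrollers could know, not estimates of what they do know.

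A reader might go further and multiply the predictable share by an assumed shift in sickness-absence risk, to state a bias against the planned 15-point difference. The documents do not support this. They give neither the size of any shift nor how often a predictable slot would be exploited, so no single bias figure should be quoted. It would also be too strong to say that the analysis is helpless, since adjustment can deal with measured imbalance; unmeasured selection is what remains out of reach.

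The point merits action because it bears on the comparability of the two arms and the remedy is cheap.

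**What to change.** For all envelopes not yet opened:

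1. Regenerate the list for each centre with randomly varying block sizes, for example 4, 6 and 8.
2. Disclose the sizes neither to centres nor in publications until recruitment ends.
3. Open each envelope only after consent and eligibility are recorded. This prevents exclusion once the arm is seen; it does not prevent selective invitation beforehand.
4. Report the date of the change, state the remaining predictability (best guess still about 68%) as a limitation, and compare baseline ÖMPSQ-SF by arm. That comparison is a weak test, because entry requires a score of at least 40 and selection could act on other features, so similar scores would not rule selection out.

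The cost is new lists and envelopes, and slightly larger possible imbalance at small centres: within a block the arms can differ by at most half the block size, so by 4 in a block of 8 against 3 now. A block cut short at the changeover can also leave a difference of up to 3 at that centre.
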